## Abstract

**Background:**

The health benefits of physical exercise have been shown to be important in the prevention of cardiovascular diseases in patients with hypertension, dyslipidaemia or diabetes. However, few strategies have demonstrated efficacy and practicality in the promotion of physical exercise among this group of patients in general practice.

**Methods:**

The PEPPER clinical study is a randomised controlled trial to evaluate the efficacy over a period of 12 months, in terms of physical activity level, of an intervention based on structured information delivery, a personalised written physical activity prescription in number of steps per day, a pedometer and a pedometer logbook, in 35 to 74-year-old patients with cardiovascular risk factors. 140 patients will be recruited in 15 GP practices and randomised in the intervention group or in the control group where patients will receive verbal advice of physical exercise. The primary outcome is the change at three months in total energy expenditure measured by an accelerometer over a 7-day period. Secondary outcomes include changes at 3 and 12 months in physical activity levels (accelerometer and International Physical Activity Questionnaire), quality of life (SF-36), blood pressure, weight, waist circumference, perceived obstacles to physical activity and patient compliance with the recommended strategy. Both groups will be compared using mixed models.

**Discussion:**

The results are expected at the end of 2019. If the intervention proves effective in durably increasing the level of physical activity, this strategy could be tested in a larger trial to examine its impact on cardiovascular diseases.

**Trial registration:**

US National Institutes of Health Clinical Trials Registry NCT02317003, December 15, 2014.

## Background

Insufficient physical activity represents the fourth highest mortality risk factor in the world with more than 3.2 million deaths annually and 32.1 million Quality Adjusted Life Year (QALY) [1]. All cause mortality risk is increased in sedentary individuals by 20 to 30% compared to individuals having moderate intensity physical activity for 30 min a day, four days a week [1]. The benefits of physical exercise are particularly significant for individuals with cardiovascular risk factors. A weekly 150 min physical activity of moderate intensity reduces the risk of developing hypercholesterolemia [2], the risk of coronary heart disease by 30%, the risk of diabetes by 27% [1], the risk of stroke by 25% [3] and of hypertension by 12% [4].

Recent cohort studies by Moore, et al. [5] and Wen, et al. [6], on large samples of hundreds of thousands of individuals in the USA, Sweden and China, have demonstrated significant benefits of physical exercise: 15 min of daily moderate intensity exercise produce a gain of 2.5 years of life compared to sedentary individuals, all cause mortality risk are reduced by 16% for active hypertensive or dyslipidaemic individuals compared to inactive individuals, and by 22% for the subgroup of diabetic or pre-diabetic patients. Both studies emphasize the high benefits of the first two hours of weekly physical exercise and have established a dose-response relationship of physical exercise: on top of 15 min of daily moderate intensity exercise, a daily additional 15 min yields a decrease of 4% of all cause mortality risk.

Various types of interventions have been evaluated over the past 15 years in order to promote physical activity and reduce sedentary lifestyle. Among the large variety of sometimes complex strategies that have been tested in the litterature, the most common, cost-effective, simple and consistently efficient components that were thought applicable to the context of this study were: patient education on the consequences of sedentary lifestyle and the benefits of physical exercise [7], a written prescription of physical exercise with measurable goals [8], encouraging early identification of barriers to behavioural change [9], self-determined objectives [10], setting graded tasks [7, 11], self-monitoring of behaviour and performance [7, 11], the use of a pedometer [12–15] and using follow-up prompts and encouragement through meetings, phone calls or messages [11]. However, in many countries, the most prevalent strategy to promote physical activity in primary care remains verbal advice to patients [16], with limited results.

Moreover, few studies have evaluated the long-term motivational effect of pedometers (beyond 6 months). As stated by the British National Institute for Clinical Excellence [17], although pedometers have shown short term efficacy, there is currently insufficient evidence to generalise their use in primary care. In addition, the most efficacious interventions are often complex, involving regular follow-up phone calls or meetings with the support of nurses or other health professionals. These strategies are, therefore, often impractical in countries like France, where general practitioners have limited support.

The aim of the present study is, therefore, to test a simple, low-cost, primary care intervention to increase the physical activity of patients with cardiovascular risk factors.

## Methods/design

### Study design

The PEPPER study is an experimental, comparative, prospective, open, multicentric controlled randomised trial in two parallel groups.

### Participants

Participants are recruited by their general practitioner (GP) in 15 GP practices in the Pays-De-La-Loire region.

Participants are 35 to 74-year-old adults, consulting their usual general practitioner (GP) for a non-urgent matter, and followed-up every three months for hypertension, hypercholesterolemia or non-insulin dependent type 2 diabetes. Patients will be judged insufficiently active by their general practitioner on the basis of at least their answers to two questions:“Do you practice any sports, including cycling, an hour or more every week?”“Does your work involve physical activities?”

The inclusion criterion is fulfilled by a negative answer to both questions.

Exclusion criteria are: having a health condition that contraindicates a moderate physical activity, as judged by the general practitioner; being unable to walk without human or material help; having any health condition, including psychiatric or cognitive impairments, that would prevent the participant from fully understanding the study and his or her doctor’s advice, as judged by the general practitioner; being unable to communicate in French, or refusing to participate.

Patients will be able to withdraw their consent or request to leave the study at any time and regardless of the reason.

The investigator can discontinue, temporarily or permanently, the participation of a patient in the study for any reason that would be in the best interest of the patient, especially in case of serious adverse events.

The exclusion of a patient is required in case of:Withdrawal of consent for participation,Serious event with consequences for the patient’s ability to follow the study protocol.

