#### Change in health status and adverse events

Data are collected at 0, 3 and 12 months regarding changes in drug treatment (stable / increased / decreased), adverse events (acute serious pathological episode, new diagnostics of chronic or serious pathologies…) and, if available, the dates and values of the latest blood tests, including total cholesterol, HDL-C, LDL-C, triglycerides and HbA1c.

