### Statistical analyses

A diagram will describe the participant selection process, with a descriptive analysis of their characteristics.

Quantitative variables will be expressed as mean ± standard deviation (median and inter-quartile interval if the normality hypothesis is not valid). Qualitative variables will be expressed as frequency and percentage.

Intention to treat analysis will be carried out, taking into account all randomised people. Multiple imputation techniques will be used to handle missing data.

An additional per-protocol analysis will also be carried out, taking into account those patients for whom the assessment criteria will be available.

The Student’s t-test (or the non-parametric Mann-Whitney U-test, depending on the variable distribution) and mixed models will be used to compare both groups for the primary outcome and for the other quantitative variables.

For qualitative variables, the Pearson’s chi-squared test (or the Fisher’s exact test, when necessary) will be used.

The level of significance is set to 0.05 and all tests are bilateral.

Bivariate analyses will be carried out for all outcomes. Additional multivariate analyses may be performed to adjust for significant factors. Backward stepwise regression techniques will be used to select confounders. Adjustment variables will include:

Sex (F/M),

Age (35-54y, 55-74y),

Education level (≤ A-level, > A-level),

BMI (< 30, ≥ 30),

Diabetes (yes/no),

Occupational rate (> 80%, ≤80%).

Living environment (urban, semi-urban, rural).

All hypotheses and tests are two-tailed.

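### Mandatory exclusion after a serious event does not separate stopping the intervention from stopping data collection, so some randomised patients may enter the intention-to-treat analysis only through imputed outcomes

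*Protocol article*

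**What the plan says.** Three parts of the protocol article bear on this point.

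- **Participants.** Exclusion is compulsory in two situations, listed together with the same consequence: "The exclusion of a patient is required in case of:Withdrawal of consent for participation,Serious event with consequences". The second situation reads in full: "Serious event with consequences for the patient’s ability to follow the study protocol". A separate, discretionary clause comes just before: "The investigator can discontinue, temporarily or permanently, the participation of a patient in the study". Neither clause says whether the 3- and 12-month assessments go on afterwards.
- **Statistical analyses.** "Intention to treat analysis will be carried out, taking into account all randomised people. Multiple imputation techniques will be used to handle missing data". The additional per-protocol analysis is limited to "taking into account those patients for whom the assessment criteria will be available".
- **Change in health status and adverse events.** "Data are collected at 0, 3 and 12 months regarding changes in drug treatment"; the same sentence covers adverse events, and acute serious episodes are among its examples.

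The Data collection section provides telephone reminders when data do not arrive. It does not mention patients who have been excluded.

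**The concern.** The exclusion rule applies to participation in the study, not to receipt of the intervention, and it puts a serious event on the same footing as withdrawn consent. Followed as written, it ends measurement for a randomised patient because of something that happened after randomisation.

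Three things are at stake.

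1. **The loss is plausibly related to outcome.** The primary outcome is accelerometer energy expenditure. An event that stops someone following an activity programme probably lowers that outcome too. If the missing value is filled in as though the event had not happened, activity in that arm is overstated.
2. **The loss may differ by arm.** The trial is open and the GP who delivers the intervention judges the event. The criterion is ability to follow the protocol, and the arms ask for different things: a step target, pedometer and logbook in PPIL, and a daily spell of brisk walking or similar activity in VA. The same event could lead to exclusion more readily in PPIL.
3. **Safety follow-up may be cut short.** The patients whose adverse-event data matter most are those the rule removes.

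**Working it through.** **Step 1. Reproduce the plan's own figure.** Inputs from Sample size: difference 105, SD 185 MET-min/week, two-sided alpha 5%, power 90%, 70 per group.

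n per group = 2 × (1.960 + 1.282)² × 185² / 105² = 2 × 10.51 × 3.104 = 65.2, so 66 (67 with the t distribution).

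With 70 per group the power is 91.9% (91.5% with the t distribution). The stated 140 is therefore adequate and slightly generous.

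**Step 2. Is precision the problem?** No dropout or exclusion rate is stated, so these losses are assumptions. Counting only observed patients:

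| Loss in each arm | Power (normal approximation) |
|---|---|
| 2% | 91.4% |
| 5% | 90.5% |
| 10% | 89.0% |
| 20% | 85.2% |

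A few exclusions cost little power. Any harm comes through bias.

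**Step 3. Size of a possible bias.** Let f be the fraction of an arm excluded and D the amount by which the excluded patients' true mean change lies below the value imputed for them. Each arm mean is overstated by f × D. With the same D in both arms:

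bias in the contrast = (f_PPIL − f_VA) × D

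For k excess exclusions in an arm of 70 this is k/70 × D. Both k and D are assumptions. D = 185 is one SD of change from Sample size, and D = 370 is two SD.

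| Excess exclusions k | D = 185 | Share of 105 | D = 370 |
|---|---|---|---|
| 0 | 0 | 0% | 0 |
| 1 | 185/70 = 2.6 | 2.5% | 5.3 |
| 3 | 3 × 185/70 = 7.9 | 7.6% | 15.9 |
| 5 | 5 × 185/70 = 13.2 | 12.6% | 26.4 |

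Excess exclusions in PPIL push the contrast towards PPIL; an excess in VA pushes it the other way.

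**Step 4. Set the passages side by side.** Participants decides who stays in the study. Statistical analyses decides who is analysed, and keeps every randomised person through imputation. Nothing removes an excluded patient from the intention-to-treat set. But if measurement has stopped, that patient contributes only an imputed value there and nothing to the per-protocol set, which needs an available outcome. On that reading neither planned analysis contains what happened to the patient after the event.

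**Step 5. Limits of the scope.** Randomisation follows the baseline self-assessment, so an exclusion before it does not touch the intention-to-treat set. Ending data collection when consent to it is withdrawn is not in question.

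**The case against.** The strongest reply is that the text is ambiguous, not wrong. The article does not say that data collection stops; the discretionary clause allows a temporary interruption; and serious episodes are within planned adverse-event collection. Much of this stands: loss of data is the natural reading, not a stated fact. It is the natural reading because the serious event is bracketed with withdrawn consent, the adjoining clause speaks of participation in the study, and no section provides for measurement after exclusion.

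Four stronger readings are tempting, and the article does not support them.

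- **That the rule contradicts intention to treat.** It does not: "Intention to treat analysis will be carried out, taking into account all randomised people". Excluded patients remain in the analysis through imputation.
- **That the imputation will be biased.** The article says only "Multiple imputation techniques will be used to handle missing data". The model, its predictors and any sensitivity analysis may properly sit in an analysis plan that is not shown. However, no such plan can recover outcomes that were never collected.
- **That the bias is large.** A gap of 500 MET-min/week with three excess exclusions would give 500 × 3/70 = 21.4, or 20% of the target. But 500 is 2.7 times the design SD (500/185) and has no source in the article.
- **That exclusions will be unbalanced.** Open allocation makes this possible. It is no evidence of how often it will happen.

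It is also fair to say that some of these patients could not wear the accelerometer or complete the questionnaires under any wording, so the rewording would recover only part of the data.

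**Conclusion.** The point holds as a defect in a stated rule, with a modest and conditional effect. The article makes exclusion compulsory after a serious event without separating the end of the intervention from the end of follow-up. On the natural reading this discards observed outcomes and adverse-event data for a reason plausibly tied to the primary outcome, on the judgement of unblinded GPs.

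With one to five excess exclusions in one arm and a one-SD gap, the primary contrast moves by about 2.6 to 13 MET-min/week against a target of 105. With equal exclusions and equal gaps it does not move, although the follow-up safety data would still be lost. The figures rest on an assumed number of excess exclusions, an assumed gap, and an imputation that takes no account of the event; the article fixes none of these. The change is worth making because it is cheap and the lost data cannot be recovered later.

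**What to change.** Reword the exclusion paragraph in Participants so that, for randomised patients, neither a serious event nor an investigator's decision to stop the intervention by itself ends data collection. Unless the patient withdraws consent to data collection or cannot be assessed, the 3- and 12-month accelerometer and questionnaire assessments and the adverse-event collection continue, and all observed data enter the intention-to-treat analysis. When to stop the intervention remains with the investigator; this change does not touch that decision.

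The cost is one revised paragraph and a small amount of extra follow-up, in patients for whom these assessments were already planned.

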### Control group (VA)

In the control group, participants who are judged insufficiently active by their GP will be verbally advised to increase their physical exercise to at least 15 min of brisk walking, or other physical activity that makes them breathe quicker than normal, every day of the week.

Doctors will deliver the intervention every three months at each follow-up consultation.

### Intervention group (PPIL)

The strategy in the intervention group involves:A written prescription of physical activity,Information on the benefits of physical activity,The loan of a pedometer,The delivery of a pedometer logbook.

#### Prescription of physical exercise

The prescription of physical exercise written by the GP states the number of steps per day above the patient’s baseline level. For example, the GP may prescribe “4000 steps above your usual number of steps”. The GP is free to adjust the prescription. The patient should agree with the prescription and should regard the objective as being achievable. The GP will encourage the patient to try and reach the prescribed goal and to define intermediate self-determined weekly goals in order to achieve the final objective in about three months. The patient and the GP will reassess the objective every three months during follow-up consultations.

#### Information on physical activity

The GP will deliver verbal and written information on the benefits of physical activity, included in the pedometer logbook given to the patient. The information is structured according to behavioural and cognitive theories of behaviour change, and refers to the following strategies as coded by Abraham and Michie [18]:Provide information on the consequences of behaviour in general, emphasising short term and long term effects,Provide information on the consequences of behaviour to the individual, in relation to the patient’s specific risk factors or pathology,5. Goal setting,8. Barrier identification/Problem solving, using the Determinant of Physical Activity Questionnaire [9] included in the logbook,9. Set graded tasks, through weekly self-determined objectives,10. Prompt review of behavioural goals, during follow-up consultations and in review of previous performances in the logbook,16. Prompt self-monitoring of behaviour, using the pedometer,19. Provide feedback on performance, during follow-up consultations.

#### Pedometer

The GP will lend a pedometer (Omron HJ-321-E) to the patient. The pedometer is tri-axial to make it easy to carry in a pocket or a bag. It has a 7-day memory and resets automatically at midnight. The GP will advise the patient to carry the pedometer as often as possible, and to regularly monitor the number of steps achieved during the day.

#### Logbook

The logbook will begin with information on the benefits of physical exercise, a simplified pedometer user manual, suggestions on how to increase the number of daily steps and a frequently asked questions section. The logbook itself will include a weekly diary where the patient records his or her self-determined weekly objective and the number of daily steps achieved, and the average number of steps achieved during the past seven days. For activities that are not well accounted for by the pedometer (swimming, cycling, lifting heavy weights…), the end of the logbook will include a table giving the equivalence in number of steps for various physical activities. The GP will encourage the patient to bring their logbook to follow-up consultations to review his or her progress.

The GP will administer the intervention at least every three months during each follow-up consultation.

### Recruitment and follow-up

GP practices are selected according to the following criteria:The GP practice is located in the pays De La Loire region in FranceThe general practitioner is a GP trainer involved in the University of Angers Medical SchoolThe general practitioner volunteers to be investigator in this study

All the investigators are briefed on the details of the study and the delivery of the interventions.

The GPs will recruit participants from among their patients who meet the inclusion criteria, and agree to participate in the study, during normal consultations. The inclusion period is set to 15 weeks and may be prolonged according to the number of participants actually recruited.

Each participant will receive by mail, after his or her inclusion, a self-assessment kit, including the accelerometer to wear for at least seven days in a row, from sunrise to sunset, and self-administered questionnaires. After the 7-day period, participants will return the self-assessment kit by mail.

Participants will then meet again with their GPs. During this second consultation, participants will be randomised to either the PPIL or the VA group and GPs will deliver the assigned intervention.

Follow-up consultations will then occur every three months during the following 12 months. Follow-up consultations at 3 and 12 months will be preceded by a 7-day self-assessment period using the accelerometer and the questionnaires. The recruitment and follow-up flowchart is given in Fig. 1.

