### Primary and secondary outcomes

The primary outcome is the change at three months of the total weekly energy expenditure, measured by an accelerometer in Metabolic Equivalent Task-minute (MET-min), compared to baseline. The accelerometer (Actigraph wGT3x-BT validated in research [19–23]) is worn at the belt over a 7-day period, from morning to bedtime. The Swartz Adult Overground & Lifestyle algorithm [24] is used to convert from accelerometer counts to MET.

The key secondary outcome is the change at 12 months of the total weekly energy expenditure, measured by an accelerometer in MET-min, compared to baseline.

The other secondary outcomes are:Change at 3 and 12 months in the weekly time dedicated to moderate and high intensity physical activity, and in the weekly physical activity level in MET-min calculated by the International Physical Activity Questionnaire (IPAQ), from baseline.Change at 3 and 12 months in the scores on the SF36 quality of life questionnaire compared to baseline.Change at 3 and 12 months to weight, waist circumference and arterial blood pressure compared to baseline,Changes in the patient’s drug treatment at 3 and 12 months,Perceived obstacles to physical activity at 3 and 12 months as assessed by the Determinants of Physical Activity Questionnaire (DPAQ),Details of the physical exercise promotion strategies applied during the study,Compliance of patients with their doctor’s recommendations.

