### Sample size

Studies by Kirk, et al. [25], Pinto, et al. [26], Baker, et al. [27] and Mutrie, et al. [28] were chosen as a base for sample sizing, considering their similarity to the PEPPER trial, their sample size and the outcomes reported. None of these studies reported measures in MET-min, but there is a linear relationship between the energy expenditure and the duration of physical activity, the step count or the raw accelerometer output: 15 min of moderate intensity physical exercise is equivalent to 45 MET-min.

Using a 2-tailed hypothesis, a sample of 140 patients in two groups of 70 will be necessary to detect a difference, between the two groups, of the change in total energy expenditure at three months of 105 MET-min/week (about 35 min of moderate intensity physical exercise per week), with an estimated standard deviation of 185 MET-min/week, an alpha risk of 5% and a power of 90%.

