#### Energy expenditure and physical activity

Energy expenditure and physical activity will be measured at 0, 3 and 12 months, by two methods:Using an accelerometer (Actigraph wGT3x-BT), worn at the waist using an elastic belt during seven consecutive days, from morning to bedtime, to measure the total weekly energy expenditure in MET-min/week, the total time spent in moderate (between 3.75 and 7.49 MET-min) and high intensity (> 7.5 MET-min) physical activities; The default energy expenditure during the time when the accelerometer is not worn will be 1 MET-min.Using the self-administered International Physical Activity Questionnaire (IPAQ) [29], short version, covering the past seven days, to measure the weekly energy expenditure in MET-min/week.

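### The protocol gives two different daily wear windows for the primary-outcome accelerometer, and because unworn time is scored as rest, the difference would reach the outcome

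*Protocol article*

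**What the plan says.** The article states the daily wear window three times, in two versions.

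- Recruitment and follow-up, describing the self-assessment kit mailed after inclusion: "the accelerometer to wear for at least seven days in a row, from sunrise to sunset".
- Primary and secondary outcomes: the device "is worn at the belt over a 7-day period, from morning to bedtime".
- Energy expenditure and physical activity, under Data collection: "worn at the waist using an elastic belt during seven consecutive days, from morning to bedtime".

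Two other statements decide whether the difference matters. The outcome is a total: "The primary outcome is the change at three months of the total weekly energy expenditure, measured by an accelerometer". Unworn time is also given a fixed value: "The default energy expenditure during the time when the accelerometer is not worn will be 1 MET-min".

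On timing: "The inclusion period is set to 15 weeks and may be prolonged according to the number of participants actually recruited", and "Follow-up consultations at 3 and 12 months will be preceded by a 7-day self-assessment period using the accelerometer and the questionnaires".

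**The concern.** Sunset and bedtime are different times of day, and the gap between them varies over the year. Nothing in the article reconciles the two versions.

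If the outcome used only worn time, or a rate per hour worn, a shorter window would matter less. Here the outcome is a weekly total with unworn time set to the resting value, so a device taken off at sunset records the whole evening as rest. Two things follow under the daylight version:

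- **Lost evening activity.** Walking after sunset, a plausible time for employed patients to meet a step target, would not be counted. Any true difference between arms that arises in the evening would be diluted.
- **A window that moves with the calendar.** Baseline and month 3 fall in different parts of the year, so the number of observed hours would change between them for reasons unrelated to activity. Season is neither a minimisation factor (Randomisation and blinding) nor a listed adjustment variable (Statistical analyses).

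**Working it through.** **Inputs from the protocol.** Target difference 105 MET-min/week, SD 185 MET-min/week, two-sided alpha 5%, power 90%, 70 per group (Sample size); 15-week inclusion period (Recruitment and follow-up); unworn time at 1 MET (Energy expenditure and physical activity).

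**Assumptions not in the protocol.** Latitude 47.3 N for the region; full adherence to a sunset rule; an average of 0.2 MET above rest in the affected hours (0.3 and 0.5 also shown); even recruitment over the 15 weeks; 91 days between the two measurements; day-length variation independent of the other variation in the outcome.

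**1. The plan's own figure.** n per arm = 2 × (1.96 + 1.2816)² × (185/105)² = 65.2, so 66 per arm, or 132 in total. The plan says "a sample of 140 patients in two groups of 70 will be necessary to detect a difference". At 70 per arm, power = Φ(105 / (185 × √(2/70)) − 1.96) = Φ(1.398) = 91.9%. The stated size is therefore adequate on its own inputs. This point does not dispute it and uses 105 and 185 only as a scale.

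**2. Cost of one unworn waking hour per day.** Loss = 7 × 60 × (true MET − 1) MET-min/week.

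| Excess over rest (assumed) | Loss per hour/day | Wear difference equal to the 105 target |
|---|---|---|
| 0.2 MET | 84 | 75 min/day |
| 0.3 MET | 126 | 50 min/day |
| 0.5 MET | 210 | 30 min/day |

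**3. How far daylight moves.** Day length = (24/π) × arccos(−tan(latitude) × tan(declination)), with declination a sinusoid of amplitude 23.44°. At 47.3 N this runs from 8.3 to 15.7 h. The change over 91 days runs from −5.0 to +5.0 h/day, depending on start date. Within a 105-day (15-week) inclusion window, the SD of that change between participants is 0.51 to 2.56 h/day, depending on when the window opens. Limiting daylight to assumed waking hours of 07:00 to 22:30 barely changes this (SD about 0.6 to 2.6 h/day).

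**4. Effect on the SD and power, at 0.2 MET.**

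- Added SD: 0.51 × 84 = 43; 2.56 × 84 = 215 MET-min/week.
- Combined SD: √(185² + 43²) = 190; √(185² + 215²) = 284.
- Power at 70 per arm: Φ(105 / (190 × √(2/70)) − 1.96) = about 91% (90.5% before rounding); Φ(105 / (284 × √(2/70)) − 1.96) = about 59%.

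Higher assumed MET values give more. At 0.3 MET the added SD is 0.51 × 126 = 64 to 2.56 × 126 = 323. At 0.5 MET it is 0.51 × 210 = 107 to 2.56 × 210 = 538.

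**5. Month 12.** Baseline and month 12 fall at about the same time of year, so the day-length change is close to zero and the seasonal part largely cancels. Evening activity would still be missed at both visits.

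**The case against.** The strongest reply is that the governing text is clear. The outcome definition and the data-collection section agree on waking hours, and the daylight phrase stands once, in a recruitment narrative, where it may simply be a loose way of saying all day. Much of this stands: the waking-hours window is evidently the intended design, and the defect is an inconsistency in wording rather than a chosen design. But the stray phrase sits where the article describes what participants receive, so the two texts still have to be reconciled.

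Four stronger readings are tempting and not supported.

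- **That season biases the comparison of arms.** Patients are randomised individually and concurrently, with the follow-up doctor among the minimisation factors. Day length depends on the calendar date and is shared by patients of both arms measured in the same week, so on average it affects both arms alike.
- **That participants were told to remove the device at sunset.** The kit's own wording is not shown. The article lists its contents and does not reproduce its instructions.
- **That the trial is underpowered.** The power loss in the working requires literal adherence to the daylight wording and rests on an assumed latitude and MET excess. The upper end of any range depends mainly on the MET value chosen.
- **That a minimum of seven days conflicts with a 7-day total.** The same section goes on to refer to a 7-day period before the kit is returned, and the choice of days to analyse is commonly left to the analysis plan.

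**Conclusion.** The contradiction is real and unreconciled, and it rests on no assumption. It is more than clerical because scoring unworn time at 1 MET within a weekly total makes the wear window part of the primary outcome.

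If the daylight wording were followed, the consequence would be added variance in the 3-month change and diluted evening activity, without an expected bias towards either arm. The figures for SD (190 to 284 against the planned 185) and power (91% to 59% against about 92%) are an illustrative upper bound under the assumptions listed. Looser adherence would give less; a higher MET excess would give more. The stated sample size of 140 is unaffected once a single waking-hours window applies throughout.

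**What to change.** In Recruitment and follow-up, replace the daylight window with the morning-to-bedtime window already used in Primary and secondary outcomes and in Energy expenditure and physical activity. Check that the instructions in the participant kit carry the same waking-hours window at baseline, month 3 and month 12.

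The cost is one phrase in the protocol and one check of the kit text, with a correction there only if it carries the daylight wording. Neither the sample size nor the analysis needs to change.
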